### Randomization and blinding

2.6

Forty-eight participants will be randomly allocated to either the DLPFC-tDCS group (Study Group) or the M1-tDCS group (Control Group). The randomization process will be conducted by a researcher who is not involved in participant recruitment, treatment, or assessment. This researcher will be instructed to keep the assigned interventions confidential from the participants, therapist, and other researchers until the study is completed. Randomization will be performed while employing the pseudo-random number generating RAND() function in Microsoft Excel, which produces random values between 0 and 1. Each generated number will then be ranked using the RANK() function in Excel, assigning a unique position to each value. The sorted random numbers will be assigned to groups, with values ranked 1–24 allocated to the Control Group and those ranked 25–48 assigned to the Study Group.

The study will follow a double-blind design, where both participants and evaluators remain unaware of group assignments until the study concludes (Figure 2). Concealed allocation will be ensured using sequentially numbered, opaque, sealed envelopes. The evaluator, trained in study procedures, will be blinded to the group assignments. Only the researcher responsible for administering the tDCS intervention will have access to group allocation. A blinding scale will be applied to both the evaluators and participants to assess the effectiveness of blinding. Furthermore, to maintain blinding for participants, they will not have access to the display interface of the stimulation intervention paradigm. According to the modified Jadad scale, this blinding belongs to a high-quality blind design.

**Figure 2 fig2:**
[figure not shown]
Schedule of participant enrolment, interventions, and assessments. DLPFC, dorsolateral prefrontal cortex; M1, primary motor cortex; tDCS, transcranial direct current stimulation.

### Masking

2.7

For practical reasons, research team members involved in delivering or supporting the interventions, including the principal investigator (PI), will not be masked. However, those responsible for conducting pre- and post-intervention assessments will remain blinded. Moreover, individuals involved in data collection and analysis will not participate in the intervention process to minimize the potential for bias.

### Intervention

2.8

The international EEG 10–20 standard localization method will be used for electrode placement. In the DLPFC-tDCS group, the anode will be positioned over the left DLPFC (F3), as previous studies have shown that this region plays a key role in inhibitory control of pain processing and shows increased activity in cLBP patients (Asada et al., 2022; Cao et al., 2022). Four cathodes will be placed at a 3.5 cm radius around F3, with a current density of approximately 0.88 mA/cm^2^ (Figure 3A).

**Figure 3 fig3:**
[figure not shown]
Electrode position of DLPFC-tDCS group **(A)** and M1-tDCS group **(B)**.

For the M1-tDCS group, the anode will be placed on the contralateral side of the most painful region, while four cathodes will be positioned at a 3.5 cm radius around C3/C4 (Figure 3B). The stimulation intensity will be gradually increased to 2 mA over the first 30 s, with a total intervention duration of 20 min per session. Each patient will undergo tDCS treatment once per day, 4 days a week, for 3 weeks.

In addition to tDCS, all participants will undergo a sling exercise program. Evaluations will be performed in four positions: prone lumbar setting, supine lumbar setting, side-lying hip abduction setting, and side-lying hip adduction setting, with weak muscle chains identified (2–3 per participant). Following the principle of progressive training, sling exercise postures—including prone bridging, supine pelvic lift, side-lying hip adduction, and side-lying hip abduction —will gradually increase in difficulty while reducing external support (as detailed in Table 1). Participants will not take analgesics or undergo any other treatments during the intervention. No pain or discomfort is expected during the sessions. The sling exercise program will be supervised by a physiotherapist with over 5 years of clinical experience. The treatment will be given once daily, 4 days per week, for 3 weeks, with 12 sessions in total.

**Table 1 tab1:** Description of sling exercise protocol.

Exercise	Exercise set up	Instruction to individual
Supine pelvic lift	Individual supine with arms parallel to body; one leg flexed with knee at 90 degree and foot on surface; narrow sling at flexed knee; Wide sling under pelvis, attached with elastic cords.	Extend knee in sling; bring another leg up parallel to other; Lift a leveled pelvis up to a straight body position.
Prone bridging	Individual prone with upper body supported on forearms; elbows directly under shoulders; narrow sling just below knee; wide sling under abdomen, attached with elastic cords.	Lift another leg from surface; lift a leveled pelvis up to a straight body position.
Side-lying hip abduction	Individual side-lying with upper body supported on shoulder; top arm parallel to body; narrow sling at knee of bottom leg; wide sling under hip, attached with elastic cords.	Lift top leg; extend bottom hip; lift up to a straight body position by pressing bottom leg into sling.
Side-lying hip adduction	Individual side-lying with upper body supported on shoulder; top arm parallel to body; narrow sling at knee of top leg; wide sling under hip, attached with elastic cords.	Lift top leg; extend bottom hip; lift up to a straight body position by pressing bottom leg into sling.

### Data collection

2.9

A blinded researcher will gather outcome data before randomization (baseline), post-intervention (3 weeks post-randomization), and during follow-up evaluations at 6 and 12 months after the intervention. Assessments will be conducted again at the post-intervention stage to evaluate immediate effects and during follow-up to assess both short- and long-term intervention outcomes. All data will be systematically documented and stored in the trial database throughout the study. Furthermore, participants will be contacted by a designated researcher *via* telephone for follow-up. If a participant fails to complete the scheduled evaluation within 2 days of the appointment, they will receive a reminder message or a follow-up call from the research team.

### Outcome assessment

2.10

#### Primary outcome measures

2.10.1

##### Pain intensity

2.10.1.1

Pain intensity will be assessed using the VAS, which ranges from 0 to 10 cm, where “0 cm” indicates no pain and “10 cm” represents unbearable pain. Moreover, the Short-Form McGill Pain Questionnaire (SFMPQ) will be used to evaluate each participant’s pain experience (Strand et al., 2008). The SFMPQ consists of 15 items divided into two categories: affective scores (4 items) and sensory scores (11 items). Each item is rated on an intensity scale from 0 to 3 (0 = none, 1 = mild, 2 = moderate, 3 = severe). Pain assessments will be conducted at all time points, including baseline, 3 weeks, 6 months, and 12 months post-randomization. Meanwhile, during the follow-up period, we will record whether the patients are using painkillers or other treatments.

##### Disability

2.10.1.2

Disability associated with cLBP will be measured using the Oswestry Disability Index (ODI), a validated tool consisting of 10 questions, each with 6 response options scored from 0 to 5. This index evaluates functional impairment in cLBP by incorporating pain and physical activity measures. Based on the total score, disability is categorized as bed-ridden (81–100%), crippled (61–80%), severe disability (41–60%), moderate disability (21–40%), or minimal disability (0–20%) (Martí-Salvador et al., 2018). Participants will be instructed to complete the questionnaire based on their condition on the day of assessment.

##### Mental health

2.10.1.3

Mental health will be assessed using the short version of the Hamilton Depression Scale (HDS) and the Hamilton Anxiety Scale (HAMA). The HDS consists of three subscales, each comprising seven items, designed to evaluate anxiety, depression, and stress over the previous week (Kaptan et al., 2012). Responses are rated on a scale from 0 to 3 (fully disagree to fully agree), with total scores indicating symptom severity: a score of 13 or higher suggests depressive symptoms, 14–27 indicates mild depression, 28–41 reflects moderate depression, and scores of 42–53 suggest high level depression. The HAMA is primarily used to evaluate the severity of anxiety symptoms in individuals with neurosis and other conditions. It evaluates 14 aspects of anxiety, including mood, depressive mood, cognitive function, insomnia, fear, tension, somatic anxiety, reproductive and urinary symptoms, gastrointestinal and digestive symptoms, respiratory symptoms, cardiovascular symptoms, sensory symptoms, and behavioral responses during social interactions (Yin et al., 2023).

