**Methods:**

This study is a randomized, double-blind, controlled trial. Forty-eight individuals aged 20 to 55 years with cLBP will be randomly assigned to receive either (1) a 3-week DLPFC-tDCS intervention (*n* = 24) or (2) a 3-week M1-tDCS intervention (*n* = 24), administered four times per week for a total of 12 sessions. Clinical outcomes will be assessed at baseline, 3 weeks, and 6 and 12 months after randomization. Primary outcomes include pain intensity, disability, and scores on the Hamilton Depression and Hamilton Anxiety scales. Secondary outcomes include surface electromyography characteristics of trunk muscles, oxygenated and deoxygenated hemoglobin concentrations in the M1 and DLPFC, and functional connectivity between these two brain regions. These outcomes will be evaluated before and after the intervention. Effect sizes and a mixed-model repeated measures analysis of variance (2 groups × 4 time points) will be calculated.

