This study primarily aims to assess the role of M1-DLPFC functional connectivity in regulating trunk muscle synergy patterns in cLBP patients. The primary hypothesis proposes that abnormal trunk muscle synergy in cLBP is associated with reduced M1-DLPFC functional connectivity. The secondary objective is to evaluate the effects of M1-tDCS and DLPFC-tDCS post-intervention and at follow-up in terms of (1) pain, (2) disability, (3) mental health, (4) surface electromyography characteristics of trunk muscles, and (5) the concentration of oxygenated and deoxygenated hemoglobin in the cerebral cortex of M1 and DLPFC. The secondary hypothesis is that DLPFC-tDCS is more effective than M1-tDCS in increasing M1-DLPFC functional connectivity and improving symptoms of depression and anxiety.

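### The name, described content and severity bands of the depression primary outcome do not agree, and the total as described cannot isolate a depression effect

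*Protocol article*

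**What the plan says.** The Abstract (Methods) gives the outcome primary status: "Primary outcomes include pain intensity, disability, and scores on the Hamilton Depression and Hamilton Anxiety scales". Section 2.10.1.3 (Mental health), under the primary outcome measures, names a short version of the Hamilton Depression Scale (HDS) alongside the Hamilton Anxiety Scale (HAMA).

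The same section then sets out the content and scoring of the HDS:

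- Content: "The HDS consists of three subscales, each comprising seven items, designed to evaluate anxiety, depression, and stress over the previous week".
- Scoring: "Responses are rated on a scale from 0 to 3 (fully disagree to fully agree), with total scores indicating symptom severity".
- Lower bands: "a score of 13 or higher suggests depressive symptoms, 14–27 indicates mild depression".
- Upper bands: "28–41 reflects moderate depression, and scores of 42–53 suggest high level depression".

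The hypothesis that draws on this outcome is the secondary one in Section 1 (Introduction): "DLPFC-tDCS is more effective than M1-tDCS in increasing M1-DLPFC functional connectivity and improving symptoms of depression and anxiety". Stress is not named there. Section 2.11.1 applies a repeated-measures analysis of variance (2 groups by 4 time points) to the primary and secondary outcomes. Nowhere does the article say that only a depression subscale of the HDS will be analysed.

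**The concern.** The section makes three statements about one instrument: what it is called, what it contains, and how its total is read. They do not fit together. A scale named for depression is described as covering three constructs in equal parts, and the sum over all three is then labelled as depression severity. The upper limit of the bands does not match the maximum that the described items produce.

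What is at stake is the interpretation of a listed primary outcome. If the total is scored as described, a group difference driven by anxiety or stress would be reported as a difference in depression. The hypothesis treats depression and anxiety as two symptom domains, and anxiety already has its own instrument in HAMA.

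**Working it through.** **Inputs (Section 2.10.1.3).** Three subscales; seven items each; item scores 0 to 3; total-score bands 14–27, 28–41 and 42–53.

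**1. Can the stated upper limit of 53 be reproduced?**

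- Items: 3 × 7 = 21. Maximum total: 21 × 3 = 63.
- One subscale: 7 × 3 = 21.
- Two subscales, or one subscale doubled: 14 × 3 = 42 or 21 × 2 = 42.
- None of 21, 42 or 63 equals 53. Since 53 / 3 = 17.67, no whole number of items scored 0 to 3 has a maximum of 53.

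The stated figure is therefore not reproduced. On the described scale, scores 54 to 63 have no band: 63 − 53 = 10 of 64 possible values.

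**2. Could the bands belong to the depression subscale alone?** No. That subscale ends at 21, so the bands 28–41 and 42–53 could not be reached.

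**3. What does the total contain?** Depression contributes 7 of 21 items (33%); anxiety and stress contribute 14 of 21 (67%). With zero on all seven depression items, the total can still reach 14 × 3 = 42, the lower limit of the top depression band.

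**4. How much might the total dilute or gain?** The article gives no subscale variances or correlations, so these are assumptions: equal variance σ² in each subscale and a common correlation r between subscales. Then

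- Var(total) = 3σ² + 6rσ², so SD(total) = σ√(3 + 6r).
- If k subscales each shift by the same amount δ, the standardised effect on the total is kδ / (σ√(3 + 6r)).
- Relative to the effect δ/σ on one subscale, the ratio is k / √(3 + 6r).

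| Subscales that improve equally | r = 0 | r = 0.5 | r = 0.7 |
|---|---|---|---|
| Depression only (k = 1) | 58% | 41% | 37% |
| Depression and anxiety (k = 2) | 115% | 82% | 75% |
| All three (k = 3) | 173% | 122% | 112% |

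The denominators are √3 = 1.732, √6 = 2.449 and √7.2 = 2.683. The total can thus be much less sensitive than the depression subscale, or more sensitive, depending on which symptoms change. In the second and third rows a difference in the total still does not show that depression has changed.

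**The case against.** The strongest reply is that a reader might infer more than the article supports, in five ways.

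- **That the score does not measure depression, or cannot respond to it.** This goes too far. Seven of the items are depression items, so the total is contaminated, not unrelated. What stands is that it cannot separate a depression effect from an anxiety or stress effect.
- **That sensitivity is certainly lost.** The 58/41/37% figures need an effect confined to depression, whereas the secondary hypothesis expects both depression and anxiety to improve. For equal effects on those two, the result runs from a 15% gain to a 25% loss. The correlations are assumed throughout.
- **That the content of the scale is settled.** The article cannot show whether the name or the description is wrong. If the Hamilton scale is in fact given and scored by its own rules, the 14-of-21 share, the dilution and the subscale overlap disappear, and a text error remains.
- **That the band gap damages the analysis.** No planned test uses the bands: the Abstract names scores, and Section 2.11.1 specifies an analysis of variance. Section 2.5.2 excludes mental illness, so totals of 54 to 63 are likely to be rare. A score of 13 is not unclassified either; the text calls it suggestive of depressive symptoms, and it lacks only a severity grade. The gap matters mainly as evidence that the description is inconsistent.
- **That anxiety is counted twice in one statistic.** The HDS and HAMA are never summed. They are separate outcomes with overlapping content, and HAMA as described also includes depressive mood.

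These limits are accepted. They do not remove the contradiction. The items, rating and bands are stated explicitly, so this is not detail that a condensed article leaves to a fuller document, and no other section corrects it.

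**Conclusion.** The point holds as an internal inconsistency with a conditional consequence.

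The inconsistency itself rests on nothing but the article: the instrument's name, its described content (21 items on three constructs, range 0 to 63) and its depression bands (ending at 53) cannot all be right.

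The consequence depends on the scale being scored as described. In that case the total cannot isolate the depression component of the secondary hypothesis, and its anxiety items overlap with HAMA. The size of any dilution or gain depends further on assumed equal variances, assumed correlations and the pattern of improvement, so no single percentage should be cited.

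The sample size is unaffected, because Section 2.5.3 bases it on the VAS. The correction should still be made, because this is a listed primary outcome and the stated scoring would allow a change in anxiety or stress to be reported as a change in depression.

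**What to change.** Identify the instrument and version actually administered, make its name, items, score range and bands agree, and state which score is the endpoint.

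- If it is the three-subscale form: rename it, analyse its depression subscale (0 to 21) as the depression outcome instead of the total, leave anxiety to HAMA, and drop the bands or correct them to the range of the score used.
- If it is the Hamilton scale: replace the description of items, rating and bands with those of the version used.

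The cost is a wording change and a check of the scoring sheet. No extra assessment, visit or participant is needed.

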#### Secondary outcome measures

2.10.2

##### Muscle synergy

2.10.2.1

Muscle synergies will be assessed using wireless surface electromyography (sEMG) (Trigno, Delsys, Inc., USA). To optimize electrode conductivity, thorough skin preparation will be performed before electrode placement. The muscle activity of the erector spinae (ES), multifidus (MF), rectus abdominis (RA), and bilateral transversus abdominis (TA) muscles will be recorded (as shown in Table 2). Electrode placement will follow the standardized guidelines recommended in previous studies (Hermens et al., 2000; Park et al., 2014). The extraction of muscle synergies will be carried out using non-negative matrix factorization (NNMF) and principal component analysis (PCA) (Bekius et al., 2020; Rabbi et al., 2020; Wang et al., 2015). The analysis will include measurements of the muscle synergies number, complexity, sparseness, clusters, and muscle networks.

**Table 2 tab2:** Placement of the sEMG electrodes.

Muscle	Electrode placement location
Transversus abdominis (TA)	Along either side of the course of the underlying muscle fibers and centered 2 cm cephalic to the pubic bone, just lateral to the midline, and parallel to the superior pubic ramus
Rectus abdominis (RA)	2 cm lateral from the midline of the umbilicus
Multifidus (MF)	A line from caudal tip posterior spinal iliac superior to the interspace between L1 and L2 interspace at the level of L5 spinous process (i.e., about 2–3 cm from the midline)
Erector spinae (ES)	2 cm lateral to the L3 level

##### Concentration of oxygenated and deoxygenated hemoglobin in the cerebral cortex

2.10.2.2

A multichannel fNIRS system (Nirsmart, Danyang Huichuang Medical Equipment Co., Ltd., China) will be used for continuous measurement and recording of changes in oxygenated hemoglobin (HbO) and deoxyhemoglobin (HbR) concentrations during task performance. The system consists of a near-infrared light source and avalanche photodiode detectors, operating at wavelengths of 730 nm and 850 nm, respectively. It has a sampling rate of 24 light sources and 41 detectors, forming 102 effective channels (Figure 4). The average source-detector distance is 3 cm (range 2.7–3.3 cm). Following the international 10–20 system for electrode placement, this study will primarily examine brain activity in the cerebral cortex of the M1 and DLPFC. The probe locations, positioned at Ar, Al, Cz, Nz, and Iz according to the 10–20 system, will be measured using an electromagnetic 3D digitizer (Patriot, Polhemus, VT, USA) on a model head. The obtained grand-averaged coordinates will then be processed with NirSpace (Danyang Huichuang Medical Equipment Co., Ltd., China) to calculate Montreal Neurological Institute (MNI) coordinates, identify the associated brain regions, and calculate the channels overlap probability (Tsuzuki et al., 2007). Further details regarding brain regions and channel distribution are provided in Supplementary material.

**Figure 4 fig4:**
[figure not shown]
The fNIRS channels arrangement across the cerebral cortex.

##### Task performance

2.10.2.3

When conducting sEMG and fNIRS assessment, the subjects performed the following tasks. Task 1: The task of quickly raising arms with both hands. Task 2: Dual-task cognitive test. Complete the dual tasks of quickly raising the left/right arm or taking steps with the left/right leg based on the Flanker task paradigm. Task 3: Balance ability assessment, left/right single-leg standing and unbalanced standing.

### Data analysis

2.11

#### Statistical analysis

2.11.1

Statistical analyses will be performed using SPSS (version 25.0, IBM, USA). Before performing descriptive statistics, the Shapiro–Wilk test will be applied to evaluate the normality of data distribution. Data following a normal distribution will be reported as mean and standard deviation (SD), while non-normally distributed data will be expressed as medians with interquartile range (IQR). Categorical variables will be summarized as percentages and frequencies. Baseline demographic and clinical characteristics will be compared between groups using appropriate statistical tests based on the data type. Continuous variables that follow normal distribution will be analyzed while using independent sample *t*-tests, whereas non-parametric Mann–Whitney *U*-tests will be applied for non-normally distributed continuous data. Categorical variables will be analyzed using chi-square tests or Fisher’s exact tests, as appropriate. Correlations between variables will be evaluated using the Pearson correlation coefficient or Spearman correlation coefficient based on the type of data. A repeated-measures analysis of variance (2 groups × 4 time points) will be performed to assess the therapeutic effects on primary and secondary outcomes. If a significant main effect was observed, *post hoc* tests with Bonferroni correction were conducted. A *p*-value of <0.05 will be considered statistically significant.

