### Summary

3.1

This study presents the protocol for an RCT designed to assess the efficacy of tDCS targeting the DLPFC in patients with cLBP. The trial aims to determine whether DLPFC-tDCS can improve activity and functional connectivity between the M1 and DLPFC. The results of this study will provide critical insights into the potential therapeutic role of DLPFC-tDCS in improving M1-DLPFC connectivity and trunk muscle synergy, forming a theoretical foundation for novel treatment approaches for cLBP. Previous research has used multivariate pattern analysis and fMRI to identify disruptions in functional connectivity among key brain networks in cLBP patients. These networks include salience, sensorimotor, the default mode, and central executive networks. Findings suggest that the rostral anterior cingulate cortex and medial prefrontal cortex may serve as critical hubs associating the default mode network with other neural circuits in individuals with cLBP (Tu et al., 2019). Furthermore, a study published in *NeuroImage* demonstrated that the DLPFC has extensive anatomical projections to M1 and that these two regions interact closely during motor tasks. This suggests that exercise-induced neuroplasticity may result from altered input from the DLPFC to M1 rather than the training effect within M1 itself (Cao et al., 2022). These findings highlight the relevance of M1-DLPFC functional connectivity in motor control and muscle coordination.

To the best of our knowledge, this study will be the first to investigate the pathological mechanisms of cLBP by examining brain connectivity and trunk muscle synergy. We hypothesize that the abnormal coordination patterns observed in trunk muscles in cLBP patients are not only a result of adaptive changes within M1 and DLPFC but also due to reduced functional connectivity between these regions. This connectivity impairment may play a key role in the neuromuscular dysregulation of trunk muscles in cLBP. By comparing the therapeutic effects of M1-tDCS and DLPFC-tDCS, we expect that M1-tDCS will primarily increase M1-supplementary motor area (SMA) connectivity, while DLPFC-tDCS will strengthen M1-DLPFC functional connectivity. This improvement in connectivity is expected to restore trunk muscle coordination and improve clinical symptoms.

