### Strengths and limitations

3.2

One of the major strengths of this protocol is that it represents one of the first clinical trials investigating the efficacy of DLPFC-targeted tDCS in patients with cLBP. If proven effective, DLPFC-tDCS could serve as a viable therapeutic option for managing cLBP. Another advantage of the study is its potential to reveal the neuroregulatory mechanisms underlying the functional connections between brain regions and their impact on trunk muscle coordination in cLBP patients.

However, there will be some limitations. A key limitation is the absence of a healthy control group. Including healthy participants would allow for a more comprehensive comparison with the M1-tDCS and DLPFC-tDCS groups, improving the interpretation of the results. Moreover, differences in the sampling rates of the two fNIRS systems used during measurements present a methodological challenge. Since the sampling rates of fNIRS and sEMG differ, direct correlation analyses between their signals cannot be performed. Instead, only data-level analyses can be conducted, which may limit the ability to fully capture the relationship between cortical activity and muscle activation patterns.

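### The only method given for linking connectivity to synergy is a correlation without an arm term: sound at baseline, open to a treatment artefact afterwards, and unable to show regulation

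*Protocol article*

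**What the plan says.** Three statements in the protocol article concern the link between connectivity and synergy.

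- **Aim (section 1, Introduction, last paragraph):** "This study primarily aims to assess the role of M1-DLPFC functional connectivity in regulating trunk muscle synergy patterns in cLBP patients".
- **Primary hypothesis (same paragraph):** "The primary hypothesis proposes that abnormal trunk muscle synergy in cLBP is associated with reduced M1-DLPFC functional connectivity".
- **Expectation (section 3.1, Summary), after stating that DLPFC stimulation will strengthen M1-DLPFC connectivity:** "This improvement in connectivity is expected to restore trunk muscle coordination and improve clinical symptoms".

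Section 2.11.1 (Statistical analysis) gives two methods that bear on these statements.

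- **For relating variables:** "Correlations between variables will be evaluated using the Pearson correlation coefficient or Spearman correlation coefficient based on the type of data".
- **For comparing arms:** "A repeated-measures analysis of variance (2 groups × 4 time points) will be performed to assess the therapeutic effects on primary and secondary outcomes".

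On timing, the Methods part of the Abstract says of the secondary outcomes (sEMG, haemoglobin and connectivity): "These outcomes will be evaluated before and after the intervention". Both measures therefore exist at baseline and after treatment. Section 3.2 adds a restriction: "Since the sampling rates of fNIRS and sEMG differ, direct correlation analyses between their signals cannot be performed". That leaves only analyses of summary measures per participant.

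**The concern.** The aim uses the language of regulation, and section 3.1 describes a chain from stimulation through connectivity to coordination. The correlation sentence is the only stated method that can connect the two measures. The analysis of variance takes each outcome by itself. Coherence and partial directed coherence (section 2.11.2) relate muscle to muscle. The general linear model (section 2.11.3) relates task to haemoglobin.

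A Pearson or Spearman coefficient has no term for arm. After treatment, the trial expects the arms to differ in connectivity, since the secondary hypothesis is that "DLPFC-tDCS is more effective than M1-tDCS in increasing M1-DLPFC functional connectivity and improving symptoms of depression and anxiety". Section 3.1 implies that coordination will follow. If arm moves both measures, a coefficient taken over all participants contains the product of the two arm differences, even when no participant's connectivity is related to that participant's own synergy.

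At stake is the interpretation of the main mechanistic result: two separate effects of stimulation could be reported as one driving the other.

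**Working it through.** **The plan's own figures.** No figure is stated for the correlation analysis. The only computed figure is the VAS sample size in section 2.5.3. With 1.48 taken as an SD and t quantiles on 19 degrees of freedom, the printed formula gives [(2.093 + 1.328) × 1.48 / 1.15]² = 19.4, so 20 per group, and 20 × 1.2 = 24 recruited per arm. It is used here only for the arm sizes.

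**Inputs.**
- 24 per arm recruited, 20 per arm evaluable (section 2.5.3), with 1:1 allocation (section 2.6).
- Significance level 0.05, two-sided (sections 2.5.3 and 2.11.1).
- Arm difference of d₁ SD in connectivity and d₂ SD in synergy. The protocol gives neither, so 0 to 1.5 SD is an assumption. For scale only, the VAS planning values give 1.15 / 1.48 = 0.78 SD, on a different outcome and if 1.48 is an SD.
- True correlation within each arm set to zero.

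**Correlation created by arm alone.** With 1:1 allocation, an arm difference d adds d²/4 to a within-arm variance of 1, and the covariance between the measures is d₁d₂/4. Hence

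r = (d₁d₂/4) / √[(1 + d₁²/4)(1 + d₂²/4)],

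which for d₁ = d₂ = d becomes (d²/4)/(1 + d²/4).

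- d = 0.5: 0.0625 / 1.0625 = 0.06
- d = 0.8: 0.16 / 1.16 = 0.14
- d = 1.0: 0.25 / 1.25 = 0.20
- d = 1.5: 0.5625 / 1.5625 = 0.36
- either shift zero: r = 0

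**How often the test rejects.** Simulated normal data, 20,000 to 40,000 trials per row, Pearson test over both arms:

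| Shift in both measures | r from arm alone | 20 per arm | 24 per arm |
|---|---|---|---|
| none | 0 | 4.9% | 5.0% |
| one measure only, 0.78 SD | 0 | 4.9% | 5.2% |
| 0.5 SD | 0.06 | 6.4% | 6.9% |
| 0.78 SD | 0.13 | 12.9% | 14.7% |
| 0.8 SD | 0.14 | 14% | 16% |
| 1.0 SD | 0.20 | 24% | 28% |
| 1.5 SD | 0.36 | 67% | 76% |

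With the partial correlation adjusted for arm, the rate is about 5% in every row. Spearman gives the same inflation as Pearson (16% at 0.8 SD and 28% at 1.0 SD with 24 per arm), so ranks do not help.

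**Hand check by Fisher's z, 48 participants.** At 1.0 SD, atanh(0.20) × √45 = 0.203 × 6.71 = 1.36, and the chance of exceeding 1.96 is P(Z > 0.60), about 27%. At 0.8 SD, 0.139 × 6.71 = 0.93, which gives P(Z > 1.03), about 15%. Both agree with the simulation.

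**Baseline.** Before treatment, randomisation leaves no systematic arm difference. This is the first row of the table: the plain correlation keeps its 5% level.

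**The case against.** The strongest reply is that the correlation sentence is generic. It names no pair of variables, no time point and no pooling of the arms. Such details are commonly left to the full protocol or the SAP, and their absence from an article is no error. A reader might infer that the protocol commits itself to a pooled post-treatment correlation that ignores arm. It does not say so.

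Four further points on that side have force.

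- The primary hypothesis is associational and describes the condition, not a treatment effect. A baseline correlation suits it.
- The artefact needs arm effects on both measures. The between-arm hypothesis in the Introduction names connectivity, depression and anxiety, but not synergy; a synergy difference is only implied in section 3.1. Both arms also receive active stimulation and the same sling exercise programme (section 2.8).
- No document says that the causal chain rests on this coefficient. Section 3.1 bases its expectation on comparing the two stimulation arms, and section 2.11.1 gives therapeutic effects to the analysis of variance.
- A reader might infer that a false link is most likely exactly when the trial's hypotheses are true. If synergy does improve through connectivity, the link is real. The artefact arises when both arm effects exist but the link does not.

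All of this stands and narrows the point. It does not remove two things. The stated method has no arm term, so its use on later data would be unsafe in a way that is easy to prevent. And the aim speaks of regulation, which no analysis in the article can show. That mismatch lies in the text itself and would remain even if the correlation were confined to baseline.

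**Conclusion.** The point holds in a limited form. The plain correlation is adequate for the associational primary hypothesis at baseline. Over both arms on post-treatment or change data, it can be produced by arm effects alone. With 24 per arm, the false-positive rate is about 7%, 16% and 28% for shifts of 0.5, 0.8 and 1.0 SD in both measures, against about 5% after adjustment for arm. The inflation is thus small for modest effects and substantial from about 0.8 SD.

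These rates assume equal shifts in both measures, normal data, no within-arm link and no missing data. The shift sizes are assumptions throughout. If only one measure differs by arm, there is no inflation.

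Separately, and whatever the shift sizes, neither the plain nor the arm-adjusted correlation can show that connectivity regulates synergy. The regulating aim has no stated analysis that could support it.

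**What to change.** In section 2.11.1:

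1. Name the connectivity-synergy pair and test the primary association at baseline.
2. For post-treatment or change data, replace the plain coefficient with a partial correlation, or a regression of synergy on connectivity, adjusted for arm and the baseline values of both measures. Report it with a 95% CI.

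In the Introduction (aim) and section 3.1 (expectation), limit the claim to association between connectivity and synergy. Adjustment for arm removes the artefact but does not supply direction, so the rewording is needed as well.

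The cost is one sentence of analysis text and one to three degrees of freedom (one for arm, up to two for the baseline values). No extra measurements are needed, since both measures are already taken before and after the intervention. The conclusion the trial can draw becomes more modest.
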